## Abstract

**Introduction:**

Type 2 diabetes mellitus (T2DM) onset before 40 years of age has a magnified lifetime risk of cardiovascular disease. Diastolic dysfunction is its earliest cardiac manifestation. Low energy diets incorporating meal replacement products can induce diabetes remission, but do not lead to improved diastolic function, unlike supervised exercise interventions. We are examining the impact of a combined low energy diet and supervised exercise intervention on T2DM remission, with peak early diastolic strain rate, a sensitive MRI-based measure, as a key secondary outcome.

**Methods and analysis:**

This prospective, randomised, two-arm, open-label, blinded-endpoint efficacy trial is being conducted in Montreal, Edmonton and Leicester. We are enrolling 100 persons 18–45 years of age within 6 years’ T2DM diagnosis, not on insulin therapy, and with obesity. During the intensive phase (12 weeks), active intervention participants adopt an 800–900 kcal/day low energy diet combining meal replacement products with some food, and receive supervised exercise training (aerobic and resistance), three times weekly. The maintenance phase (12 weeks) focuses on sustaining any weight loss and exercise practices achieved during the intensive phase; products and exercise supervision are tapered but reinstituted, as applicable, with weight regain and/or exercise reduction. The control arm receives standard care. The primary outcome is T2DM remission, (haemoglobin A1c of less than 6.5% at 24 weeks, without use of glucose-lowering medications during maintenance). Analysis of remission will be by intention to treat with stratified Fisher’s exact test statistics.

**Ethics and dissemination:**

The trial is approved in Leicester (East Midlands – Nottingham Research Ethics Committee (21/EM/0026)), Montreal (McGill University Health Centre Research Ethics Board (RESET for remission/2021-7148)) and Edmonton (University of Alberta Health Research Ethics Board (Pro00101088). Findings will be shared widely (publications, presentations, press releases, social media platforms) and will inform an effectiveness trial.

**Trial registration number:**

ISRCTN15487120.

STRENGTHS AND LIMITATIONS OF THIS STUDYRESET will evaluate diabetes remission alongside MRI-assessed diastolic function, an early indicator of the adverse impacts of type 2 diabetes, following a low energy diet and supervised exercise.RESET will not distinguish the impacts of the individual dietary and exercise components.We are focusing on young adults with type 2 diabetes, a group at elevated risk for diabetes complications.Recruitment will be challenging due to competing responsibilities and lower numbers of young persons with type 2 diabetes compared with older age groups.

## Background

The global prevalence of diabetes over 9% and is expect to surpass 10% by 2030.^1^ More than 90% is type 2 diabetes mellitus (T2DM). Diabetes is diagnosed in over 8% of Canadians and 6% of persons in the UK. The Da Qing T2DM prevention trial’s 30-year follow-up demonstrated each year without T2DM translates into fewer cardiovascular disease (CVD) events.^2^ T2DM remission is emerging as a potential goal in early-onset disease, defined as an A1C below diagnostic thresholds without glucose-lowering medications.

Health behaviour-based remission trials to date have focused on meal-replacement facilitated lowering of energy intake combined with exercise counselling.^3–6^ The Look AHEAD (Action for Health in Diabetes) trial implemented a 1200–1800 kcal diet and an exercise target of 175 min/week. Its primary aim was reducing T2DM-related complications; remission, a secondary outcome, was 11.5% at 1 year and 7.3% at 4 years^7^; increased fitness predicted T2DM remission.^7^ The DiRECT trial (Diabetes REmission Clinical Trial)^8–10^ focused on remission within 6 years of a T2DM diagnosis through an 800 kcal meal replacement diet for 3–5 months, followed by a food-based weight maintenance diet. Participants received a step counter and were advised to increase their steps. Remission was 46% remission at 1 year^9^ and over 30% at 2 years.^10^ The DIADEM-I trial (Diabetes Intervention Accentuating Diet and Enhancing Metabolism) also focused on remission, among adults within 3 years of diagnosis through a dietary strategy similar to DiRECT but with more regular exercise counselling, incorporating both time and step goals as well as a goal of resistance training twice per week. DIADEM-I achieved over 60% remission at 1 year.^11^

Our RESET for REMISSION trial combines a meal replacement-facilitated dietary intervention with a supervised exercise intervention. Such interventions in T2DM demonstrated greater glycaemic lowering than unsupervised, counselling-based approaches,^12^ with A1C lowering independent of weight loss^13^ and conferring direct cardiac benefits in T2DM.^14 15^ Isolated diastolic dysfunction as the earliest manifestation^16^ of the concentric remodelling that typifies diabetic heart disease.^17^ In the DIASTOLIC trial^18^ (Diabetes Interventional Assessment of Slimming or Training tO Lessen Inconspicuous Cardiovascular Dysfunction), our UK team members compared low energy meal replacement diets against thrice weekly supervised aerobic exercise training over 12 weeks among young adults with T2DM to examine impacts on cardiovascular function, with remission as a secondary outcome. Seventy percent of those in the diet arm achieved remission, without impact on diastolic function; the exercise arm had little impact on remission but improved peak early diastolic strain rate,^18^ a sensitive MRI-based diastolic function measure. In RESET for REMISSION, we will combine the dietary and exercise interventions and assess impacts not only on remission but also on MRI-based measures of cardiac function, another novel aspect of our trial. Moreover, in contrast to DIASTOLIC, we will combine supervised aerobic and resistance training to optimise lean mass preservation^19^ with weight loss, and the potential for greater reductions in A1C than those observed for supervised aerobic exercise alone.^19^
^20^ We hypothesise that this combination of a low energy meal replacement based diet and supervision for both aerobic and resistance training will have synergistic impacts on remission, enhance heart health, preserve lean mass and improve fitness.^19–21^

Diastolic dysfunction is more prevalent in younger adults with T2DM compared with weight matched and lean controls.^22 23^ Compared with later-onset T2DM^24^ and even type 1 diabetes,^25^ young-onset T2DM has a more aggressive phenotype.^26^ Younger adults represent at least 16% of T2DM internationally.^27^ LookAHEAD studied persons 45–76 years of age and the average age in DiRECT was 53 years. DIADEM-I in contrast targeted adults 18–50 years of age. RESET for REMISSION will focus on those 18–45 years of age in cities in Canada and the UK. Even temporary T2DM remission could lead to fewer diabetes-related complications during what are supposed to be the most productive years.

### Aims

Among adults 18–45 years of age with obesity, within 6 years of a T2DM diagnosis, and not on insulin therapy, we will quantify the remission efficacy of a 12-week low energy diet combined with supervised exercise, followed by a 12-week phase of weight and exercise maintenance. We define T2DM remission as a haemoglobin A1c (HbA1c) value less than 6.5% (48 mmol/mol) at 24 weeks, without use of antihyperglycaemic medications during the prior 12 weeks, concordant with the international consensus definition.^3–6^

Through comprehensive cardiovascular MR (CMR), we are also assessing circumferential peak early diastolic strain rate, a sensitive measure^22^ with excellent test–retest reproducibility^28^; end-diastolic mass to volume ratio, a marker of concentric left ventricular remodelling^29^; and measures of aortic distensibility, a key determinant of concentric remodelling in T2DM.^29^ We will also ascertain impacts on a range of other measures (table 1) of insulin resistance, fitness, adiposity, cardiorenal parameters, diet, physical activity, mood and quality of life. We will evaluate participant perspectives (online supplemental appendix 1). Our results will guide the design of a longer-term effectiveness trial.

10.1136/bmjopen-2022-063888.supp1Supplementary data

**Table 1 T1:** Outcomes

	Week 12	Week 24
Primary outcome		
Diabetes remission at 24 weeks		X
Key secondary outcomes		
Other remission, glycaemic and insulin resistance measures		
Diabetes remission at 12 weeks	X	
Haemoglobin A1c, fasting glucose and insulin, Homeostatic Model Assessment for Insulin Resistance	X	X
Main CMR measures		
Left ventricular peak early diastolic strain rate (circumferential and longitudinal, MRI)		X
End-diastolic mass to volume ratio		X
Main fitness measure		
VO_2_ peak	X	X
Main fat and lean mass measures		
Total fat and lean soft tissue mass (DXA)	X	X
Weight and BMI	X	X
Cardiometabolic indicators		
Hypertension remission, systolic and diastolic blood pressure, heart rate	X	X
Total cholesterol, HDL, LDL, triglycerides	X	X
Other secondary outcomes		
Renal function measures		
Creatinine and estimated glomerular filtration rate	X	X
Urine albumin to creatinine ratio	X	X
Hepatic function measures		
Includes alanine aminotransferase (ALT) and bilirubin	X	X
Depression, anxiety and distress		
Hospital Anxiety and Depression Scale and Diabetes Distress Scale	X	X
Indirect calorimetry		
Resting metabolic rate	X	X
Additional cardiac and aortic MRI-based measures		
Longitudinal and circumferential measures of systolic strain, end systolic volume, ejection fraction, mean T1 time		X
Cross-sectional areas and distensibility of ascending and descending aortae		X
Additional measures of muscle mass and adiposity		
Neck, hip and waist circumference	X	X
Visceral adipose tissue, pancreatic and liver fat percentages, subcutaneous adipose tissue, muscle mass (MRI)		X
Dietary variables		
Total energy and macronutrient intake (protein, carbohydrates, lipids)	X	X
Selected carbohydrate types (total sugars, starch, fibre), selected lipid types (saturated, monounsaturated, polyunsaturated, cholesterol), alcohol	X	X
Accelerometer-based physical activity measures and sleep (daily average)		
Steps, overall acceleration, and intensity gradient metric	X	X
Minutes for each of sedentary, light and moderate to vigorous physical activity	X	X
Sleep time, duration of night, sleep efficiency (sleep time/duration of night)	X	X
Other exercise stress test measures		
VCO_2_ peak, maximum gradient achieved	X	X
Tertiary outcomes		
Bone measures		
Total bone mineral density and bone mineral content (DXA)	X	X
Physical function		
Handgrip strength	X	X
Short Physical Performance Battery	X	X
Dyspnoea scale	X	X
Overall health state		
EuroQuol group 5-Dimensional 5-Level Questionnaire	X	X
WHO Disability Assessment Schedule 2.0	X	X
Process evaluation		
Acceptability, feasibility, facilitators, barriers and adherence to the intervention will be determined through interviews		X

BMI, body mass index; CMR, cardiovascular MR; DXA, Dual-energy X-ray absorptiometry; HDL, High-density lipoprotein; LDL, Low-density lipoprotein.

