#### T2DM remission and related measures

The primary remission outcome requires a HbA1c below 6.5% at intervention period end, without glucose-lowering medication during the prior 12 weeks.^3–6^ Venous blood is sampled for HbA1c (high-performance liquid chromatography) measurement. Other related outcomes include HbA1c as a continuous variable, Homeostatic Model Assessment for Insulin Resistance and midpoint remission.

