##### Physician review

The study physician meets with the intervention arm participant to discuss antihyperglycaemic and antihypertensive medication withdrawal,^47^ given immediate lowering of glucose values and blood pressure with the dietary intervention. Glucagon-like peptide 1 receptors are stopped 1 week prior to the low energy diet. All other antihyperglycaemic medications are stopped the day that the diet is started. Except for ACE inhibitors or angiotensin receptor blockers prescribed for albuminuria (ie, RAAS blockade), participants stop antihypertensive medications on the day that the diet is initiated.

At weeks 1 and 2 follow-up (virtual or in-person), the physician reviews participant-recorded glucose and blood pressure data. Participants perform capillary blood glucose testing daily before breakfast and, on 1 day prior to physician follow-up, a 7-point glucose profile (measures before and 2 hours after food or meal replacement consumption and at bedtime). Antihyperglycaemic medications are not considered for reintroduction unless fasting morning capillary glucose is frequently 10 mmol/L or higher. Using the home blood pressure monitor provided, participants measure seated blood pressure each morning, after a 5 min rest period (second of two sequential measures). Antihypertensive agents are not be reintroduced unless systolic blood pressure values are generally 165 mm Hg or higher, as in the DiRECT trial.^48^ RAAS blockade may be interrupted with symptomatic hypotension.

Participants who may become pregnant are required to use reliable contraception. This is discussed, with referral as needed.

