##### Physician monitoring

The study physician meets with participants at weeks 14 and 18. The thresholds for medication adjustment are as described previously. The HbA1c value at the intermediary evaluation may also be used to guide treatment.

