### Control group

The control group receives care from their usual physician, in accordance with National Institute for Health and Care Excellence^53^ and Diabetes Canada^54^ guidelines. Following final evaluations, control arm participants will be offered a 12-week low energy diet intervention followed by a 4-week food reintroduction period.

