### Statistical analyses

Our primary outcome measures the proportion of remission in the intervention arm relative to the control arm. We will apply intention-to-treat principles for the primary outcome, assuming that remission of diabetes did not occur if information is not available. Based on the DiRECT and DIADEM-I trials, we estimate that remission counts in the control arm could be less than 2. We will therefore use stratified Fisher’s exact test statistics (ie, stratification by country and by sex) if remission counts are low in the control arm but consider Pearson χ^2^ test, if appropriate. If numbers permit, logistic ORs with 95% CIs (exact method) will also be performed to further quantify the efficacy of intervention over the control group, after adjusting for factors used to stratify the randomisation (country, age or sex); we will not have missing values for these covariates. Subgroup analyses for the primary outcome will be performed by country, sex and the degree of weight loss (<5%, 5%–10%, 10%–15%, >15% as examined in the DiRECT trial,^9^ collapsing categories as needed, and by exercise adherence (<50%, >50% of supervised sessions attended). In a per-protocol analysis, we will restrict the intervention group to those who achieved at least 10% wt loss and adhered to at least two thirds of prescribed exercise sessions.

We will analyse dichotomous secondary outcomes (eg, diabetes remission at 12 weeks, hypertension remission at 12 and 24 weeks) as described for the primary outcome. We will analyse continuous key secondary outcomes (eg, left ventricular peak early diastolic strain rate, lean soft tissue mass) through linear regression or log-linear regression, as appropriate, with stratification by country and sex.

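### The continuous glycaemic outcomes compare diet, exercise and drug withdrawal with usual care; read as the effect of diet plus exercise, HbA1c and fasting glucose differences are pulled toward zero in participants on drugs at entry

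*Protocol article*

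**What the plan says.** All references are to the protocol article.

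- **Outcomes.** Table 1, under Aims, puts "Haemoglobin A1c, fasting glucose and insulin, Homeostatic Model Assessment for Insulin Resistance" among the key secondary outcomes at weeks 12 and 24. The section on T2DM remission and related measures confirms the continuous form: "Other related outcomes include HbA1c as a continuous variable, Homeostatic Model Assessment for Insulin Resistance and midpoint remission".
- **Intervention arm.** Under Experimental group, Physician review (first two weeks), GLP-1 agents stop a week before the diet. For the rest: "All other antihyperglycaemic medications are stopped the day that the diet is started". Restart is restricted: "Antihyperglycaemic medications are not considered for reintroduction unless fasting morning capillary glucose is frequently 10 mmol/L or higher". In the maintenance phase the thresholds carry over, and "The HbA1c value at the intermediary evaluation may also be used to guide treatment".
- **Control arm.** "The control group receives care from their usual physician", under national guidelines. No withdrawal is described.
- **Eligibility.** Table 2 admits both drug users and non-users, with an HbA1c floor of 6% for users and 6.5% for non-users. Drug status at entry is therefore known for everyone.
- **Analysis.** Continuous key secondary outcomes are analysed by "linear regression or log-linear regression, as appropriate, with stratification by country and sex". Glucose-lowering medication is not mentioned for them.

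**The concern.** Among participants on drugs at entry, the arms differ by protocol in two respects: one arm receives diet and exercise, and the same arm loses its drugs. For HbA1c and fasting glucose these act in opposite directions, so the regression coefficient is their net effect.

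The Aims section sets out to quantify the remission efficacy of a low energy diet with supervised exercise. The Background motivates the design partly by the glucose-lowering effect of exercise. A reader will naturally take the HbA1c result as the glycaemic effect of diet plus exercise.

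The remission outcomes deal with drug use through their definition; the continuous measures have no equivalent. The two can also diverge. A control who stays on drugs cannot count as a remitter, which widens the remission contrast. The same drugs lower that control's HbA1c, which narrows the HbA1c contrast. A clear remission result beside a modest HbA1c difference is therefore foreseeable, and it could be misread as little glycaemic benefit.

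**Working it through.** **No figure to reproduce.** The Sample size section gives no effect, SD or power for HbA1c, glucose, insulin or HOMA-IR. Apart from the 35 completers per arm, every input below is an assumption.

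**Step 1: direction.**
- HbA1c and fasting glucose: removing a glucose-lowering drug raises both. Among baseline users, withdrawal in one arm only moves the difference toward zero. Intensified treatment in controls would act the same way; reintroduction in the intervention arm acts against it.
- Fasting insulin and HOMA-IR: stopping a drug that raises insulin secretion would lower insulin, and stopping an insulin sensitiser would raise it. The article does not give the drug mix, so the sign is open.
- Participants on no drugs at entry: the initial stop cannot act.

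**Step 2: possible size for HbA1c.** Let m be the share on drugs at entry, r the share of those whose drugs are reintroduced, and e the HbA1c effect of the withdrawn drugs. Assume the drug effect adds fully to the diet effect and that control treatment is unchanged. Then

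shift = m × (1 − r) × e

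| Case | m | r | e (points) | Shift (points) |
|---|---|---|---|---|
| Low | 0.5 | 0.4 | 0.5 | 0.15 |
| Middle | 0.7 | 0.2 | 0.5 | 0.28 |
| High | 0.9 | 0 | 1.0 | 0.90 |
| Nobody on drugs | 0 | – | any | 0 |

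**Step 3: consequence (purely illustrative).** Suppose the difference at equal medication were 1.0 point, with SD 1.2, 35 per arm and two-sided 5%. The standard error is 1.2 × √(2/35) = 0.287, and power ≈ Φ(difference/0.287 − 1.96):
- no shift, difference 1.00: 94%
- shift 0.15, difference 0.85: 84%
- shift 0.35, difference 0.65: 62%
- shift 0.50, difference 0.50: 41%

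The trial is not sized on HbA1c, so these figures show only that a shift within the assumed range could matter.

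**Step 4: what a contrast by baseline drug use can deliver.** With 70 completers and m between 0.5 and 0.9, the no-drug group is 70 × 0.5 = 35 down to 70 × 0.1 = 7 people, or 17.5 down to 3.5 per arm. At an assumed SD of 1.0, the 95% half-width for the arm difference in that group is:
- 1.96 × √(2/17.5) = 0.66 points
- 1.96 × √(2/3.5) = 1.48 points

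These use the normal quantile; the t quantile would widen them. The estimate can support interpretation but cannot settle the question.

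**The case against.** The strongest objection is that nothing is biased. Withdrawal is described under the experimental group, so it belongs to the assigned strategy, and the regression validly estimates that strategy against usual care. This stands. A reader might infer that the planned analysis is wrong, or that it understates the treatment effect outright. The document does not support that: the shift toward zero exists only for the narrower question of diet plus exercise at equal medication.

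A reader might also infer that all four outcomes are shifted toward no effect. That is not supported for fasting insulin and HOMA-IR, whose direction is undetermined.

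Other points stand in part:
- The statistical analysis plan is not shown and may define the contrast or add covariates. The article's wording does not exclude further terms, and its named examples are strain rate and lean mass. Silence alone would be weak evidence. What remains is that the stated aim and the stated model invite different readings.
- The size is assumption throughout, including full additivity with a low energy diet.
- The no-drug contrast is imprecise. That group entered under a higher HbA1c floor, so its result need not carry over to drug users, and some of its controls may start drugs during follow-up.
- The primary outcome already headlines drug-free glycaemia, which limits the scope for misreading.

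These points reduce the concern to interpretation and a modest addition to the analysis. They do not remove it, because drug status at entry is known for everyone and using it costs almost nothing.

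**Conclusion.** The point holds in limited form. The contrast in the continuous glycaemic outcomes is a valid comparison of strategies: diet, exercise and drug withdrawal versus usual care. Taken as the effect of diet plus exercise, the HbA1c and fasting glucose differences are pulled toward zero among participants on drugs at entry. For insulin and HOMA-IR the contrast is mixed, with no fixed direction.

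The sign for HbA1c and glucose follows from the protocol. The size does not: 0.15 to 0.90 HbA1c points rests wholly on assumed drug use (50% to 90%), drug effect (0.5 to 1.0 points) and reintroduction (0% to 40%). This is a worthwhile improvement to analysis and reporting. It is not an error in the randomised comparison, and it does not affect the primary outcome.

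**What to change.** In Statistical analyses:

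1. Add baseline glucose-lowering drug use (yes/no) as a covariate in the regressions for HbA1c, fasting glucose, fasting insulin and HOMA-IR. Randomisation is stratified by country and sex, not by drug use, so this also deals with chance imbalance. By itself it does not separate withdrawal from diet plus exercise.
2. As a supportive, exploratory analysis, report the treatment contrast by baseline drug use with confidence intervals. State that the no-drug group will be small, entered under a different HbA1c floor, and may include controls who start drugs.
3. Describe the all-participant contrast as one of strategies including drug withdrawal, and show glucose-lowering drug use by arm at weeks 12 and 24 beside each glycaemic result.

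Do not adjust for post-randomisation drug use: it is affected by allocation and by the glycaemic response itself.

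The cost is a change of wording, one covariate, one extra model and one table. Baseline drug status is already established at eligibility. The downside is an imprecise subgroup estimate that must be presented as such. No change to clinical management is implied.
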